## Abstract

**Background:**

The ANCA-associated vasculitides (AAV) are systemic autoimmune inflammatory disorders characterised by necrotising inflammation affecting small to medium-sized blood vessels. Despite improvements in survival, infection and cardiovascular disease remain leading causes of morbidity and mortality.

Considerable evidence suggests that CD4 + CD28null T-cell expansions, predominantly seen in Cytomegalovirus (CMV) seropositive individuals, are associated with systemic dysregulation of immune function leading to a heightened risk of infection and cardiovascular disease. In patients with AAV, CD4 + CD28null expansions are driven by CMV and are associated with an increased risk of infection and mortality.

The aim of this study is to explore in detail the ways in which CMV modulates the immune system and to determine whether treatment with valaciclovir blocks subclinical CMV reactivation in CMV seropositive AAV patients and ameliorates the CMV-induced adverse effects on the immune system.

**Methods/design:**

CANVAS is a single-centre prospective open-label randomised controlled proof-of-concept trial of 50 adult CMV seropositive patients with stable AAV. Participants will be randomly allocated to receive valaciclovir orally (2 g QDS or reduced according to renal function) or no additional treatment for 6 months with an additional 6-month follow-up period. The primary outcome is the proportion of patients with CMV reactivation, as assessed by measurable viral load on quantitative blood and urine CMV polymerase chain reaction. The secondary outcomes are safety, change in the proportion of CD4+ CMV-specific T-cell population (defined as CD4 + CD28null cells) and change in soluble markers of inflammation from baseline to 6 months. Further tertiary and exploratory outcomes include persistence of the effect of valaciclovir on the proportion of CD4 + CD28null cells at 6 months post completion of treatment, change in the immune phenotype of CD4+ T cells and change in blood pressure and arterial stiffness parameters from baseline to 6 months.

**Discussion:**

The results of this study will enable larger studies to be conducted to determine whether by controlling subclinical CMV reactivation, we can improve clinical endpoints such as infection and cardiovascular disease. The potential impact of this study is not limited to AAV, as CD4 + CD28null cells have been linked to adverse outcomes in other inflammatory conditions and in the context of an ageing immune system.

**Trial registration:**

ClinicalTrials.gov Identifier NCT01633476 (registered 29 June 2012).

**Electronic supplementary material:**

The online version of this article (doi:10.1186/s13063-016-1482-2) contains supplementary material, which is available to authorized users.

## Background

The anti-neutrophil cytoplasmic antibody (ANCA) associated vasculitides (AAV) are a group of rare systemic autoimmune inflammatory chronic disorders that include granulomatosis with polyangiitis (Wegener’s granulomatosis) [1], microscopic polyangiitis, renal limited vasculitis and eosinophilic granulomatosis with polyangiitis (Churg–Strauss syndrome) [2]. AAV are characterised by necrotising inflammation affecting small to medium-sized blood vessels leading to end organ damage commonly affecting the kidneys, lungs and upper airways. They range in severity from localised disease affecting the upper airways to life-threatening involvement giving rise to multi-organ failure [3].

Over the last few decades, survival has greatly improved from 20 % at 2 years to 78 % at 5 years following diagnosis [4, 5]. However, survival remains below that of the healthy population with infection, cardiovascular disease (CVD) and malignancy being the most common causes of death.

Recently the role of T cells in AAV pathophysiology and exacerbation of tissue damage has gained attention. An increased percentage of CD4 T cells that have lost expression of the co-stimulatory molecule CD28 (CD4 + CD28null cells) have been reported in AAV [6]. Loss of CD28 implies repeated antigen exposure and, in a previous study, we demonstrated that this phenotype in AAV is driven by latent Cytomegalovirus (CMV) infection [7]. An expanded CD4 + CD28null cell population in this study was associated with an increased risk of infection and increased mortality in patients with AAV. In renal transplant recipients, the presence of CD4 + CD28null cell expansions is associated with a reduced response to antigenic challenge [8] and in elderly donors this pattern is also associated with frailty, reduced response to the influenza vaccine and increased mortality [9, 10]. In addition, CMV has been linked to a declining immune system associated with advancing age, a concept termed ‘immunosenescence’ [11].

Furthermore, latent CMV infection has recently been linked to increased arterial stiffness, a marker of CVD risk, in patients with chronic kidney disease (CKD) [12]. CD4 + CD28null cell expansions in turn have been associated with an increased risk of CVD in patients with CKD as well as rheumatoid arthritis [13, 14]. Finally, in vitro experiments have demonstrated that CD4+ CMV-specific cells are able to target and damage the endothelium via expression of the chemokine receptors CX3C-chemokine-receptor-1 (CX3CR1) and CXCR3 that bind their respective ligands fractalkine and interferon gamma-induced protein 10 (IP-10), which are expressed on the surface of activated endothelial cells [15]. As such, considerable evidence suggests that CMV-specific CD4 + CD28null cell expansions are associated with systemic impairment and dysregulation of immune function leading to a heightened risk of infection and CVD, two of the leading causes of morbidity and mortality in AAV patients.

CMV reactivation is believed to occur in a relatively frequent basis in vivo [16–18] and is thought to result in gradual accumulation of CD4 + CD28null CMV-specific effector T cells and a reduction in CD4+ naive T cells, a phenomenon known as ‘memory inflation’ [19]. The cytokine production of CMV-specific cells may also be modulated over time correlating to loss of function. In a study of elderly CMV seropositive patients, up to 50 % of CMV-specific CD4+ T cells were unable to produce interleukin-2 (IL-2) and were capable of only interferon gamma (IFN-γ) production [20]. Associated with cytokine modulation is an increase in the expression of inhibitory receptors, cytotoxic T-lymphocyte associated protein 4 (CTLA-4), programmed cell death protein 1 (PD-1) and T-cell immunoglobulin and mucin domain containing 3 (TIM-3) leading to attenuation of virus-specific T-cell function [21]. On the other hand, several studies have described CD4 + CD28null cells as a pro-inflammatory cytotoxic subset capable of producing significant amounts of IFN-γ, granzyme B and perforin, which are implicated in endothelial damage and an increased risk of CVD as alluded to earlier [22].

Prophylactic treatment with the anti-viral agent valaciclovir can suppress CMV replication in renal transplant recipients [23] and treatment of viraemia reduces PD-1 expression and increases IL-2 production [24]. We hypothesise that repeated episodes of sub-clinical CMV replication in AAV patients drive the expansion and possible functional impairment of CD4 + CD28null CMV-specific cells with a resultant increased susceptibility to infection. We further hypothesise that inhibition of viral replication with valaciclovir will ameliorate the expansion of CD4 + CD28null cells and possibly increase the functional capacity of the immune system in patients with AAV.

We report here the study protocol for a randomised controlled open-label proof-of-concept clinical trial that aims to explore the ways in which CMV modulates the immune system in patients with AAV and investigate whether treatment with valaciclovir can ameliorate this CMV-induced adverse modulation of the immune system.

## Methods/design

This is a single-centre open-label randomised controlled trial of oral valaciclovir treatment (2 g four times a day; reduced appropriately depending on renal function) for 6 months versus no additional treatment, in CMV seropositive patients with stable AAV, followed by a 6-month follow-up period. No placebo will be used.

The primary outcome is the proportion of patients with CMV reactivation, as assessed by measurable viral load on quantitative blood and urine CMV polymerase chain reaction (PCR). The secondary outcomes are safety, as defined by adverse events sufficient to stop treatment with valaciclovir, change in the proportion of the CD4+ CMV-specific T-cell population (defined as CD4 + CD28null cells) and change in soluble markers of inflammation from baseline to 6 months (Table 1). Further tertiary and exploratory outcomes include persistence of the effect of valaciclovir on the proportion of CD4 + CD28null cells at 6 months post completion of treatment, change in the immune phenotype of CD4+ T cells and change in blood pressure and arterial stiffness parameters from baseline to 6 months (Table 1).

**Table 1 Tab1:** Study endpoints

	Description	Specific measurement variable
Primary outcome		
	Proportion of patients with CMV reactivation	Quantification of viral DNA copies in blood and urine by quantitative polymerase chain reaction (qPCR)
Secondary outcomes		
	Safety	Number of adverse events and incidence of events by system organ class
		Adverse events sufficient to stop treatment with study drug
	Change in the proportion of CD4 + CD28null cells from baseline to 6 months	Proportion of CD3 + CD4 + CD28- T cells in peripheral blood
	Change in the concentration of soluble markers of inflammation from baseline to 6 months	Concentration of IL-2, tumour necrosis factor alpha (TNF-α), IFN-γ, IL-6, IL-10, IL-17 and highly sensitive C-reactive protein (CRP) in peripheral blood
Tertiary outcome		
	Persistence of valaciclovir effect on the proportion of CD4 + CD28null cells from 6 months to 12 months	Proportion of CD3 + CD4 + CD28- T cells in peripheral blood
Exploratory outcomes		
	Change in immune phenotype of CD4+ T cells from baseline to 6 months	Proportion of CD4 + CD28null cells secreting IFN-γ, IL-2, TNF-α, IL-5 and IL-10 in response to CMV lysate stimulation
		Proportion of CD4 + CD28null cells expressing the inhibitory receptors PD-1, TIM-3, CTLA-4 and lymphocyte activation gene 3 (LAG-3)
		Proportion of CD4 + CD28null cells expressing the transcription factors T box expressed in T cells (T-bet) and positive regulatory (PR) domain zinc finger protein 1 (BLIMP-1)
		Proportion of CD4 + CD28null cells expressing the chemokine receptors CX3CR1, CXCR3, C-C chemokine receptor type 5 (CCR5), CD49d and CD11b
		Proportion of CD4+ naive, central memory, effector memory and terminally differentiated effector memory populations
	Change in soluble markers of endothelial damage from baseline to 6 months	Concentration of fractalkine, IP-10, regulated on activation, normal T cell expressed and secreted (RANTES), P-selectin, E-selectin, monocyte chemoattractant protein-1 (MCP-1), soluble vascular cell adhesion molecule 1 (sVCAM-1) and soluble intracellular cell adhesion molecule 1 (sICAM-1) in peripheral blood
	Change in markers of arterial stiffness from baseline to 6 months	Measures of arterial stiffness: cfPWV, peripheral pulse pressure and central pulse pressure

Clinical trial authorisation has been obtained from the Medicines and Healthcare Products Regulatory Agency (MHRA) (EudraCT number 2012-001970-28). The trial sponsor is the University of Birmingham and the study will be run through the National Institute for Health Research (NIHR) and Wellcome Trust (WT) Clinical Research Facility (CRF) at the University Hospital Birmingham (UHB) National Health Service (NHS) Foundation Trust, which also hosts the UHB Vasculitis Clinic. The trial is funded by WT and Vasculitis UK. The trial will be coordinated by the trial management group (TMG) in conjunction with the NIHR/WT CRF according to the current guidelines for Good Clinical Practice (GCP) and ensuring protection of patients’ rights as detailed in the Declaration of Helsinki. All laboratory assays will be carried out in laboratories that fulfil the principles of Good Laboratory Practice and assays informing the primary and secondary outcomes will be fully validated prior to study commencement. The protocol was designed based on the SPIRIT guidelines (see SPIRIT checklist; Additional file 1).

### Participants

In total, 50 CMV seropositive patients with AAV in stable remission for 6 months or longer and on a maximum of two immunosuppressant agents will be recruited from the Vasculitis Clinic at UHB NHS Foundation Trust. Recruitment will take place over 2 years. Our tertiary referral vasculitis clinic has more than 200 patients under long-term follow-up. Approximately 90 % of patients are in remission at any one time and 70 % are seropositive for CMV. CMV status is checked routinely at the patient’s first attendance in the clinic. We anticipate that 125 of our patients attending the clinic will be eligible for this study. Recruitment of 40 % would achieve the target of 50 patients. This is a conservative rate given our previous experience. Patients will be approached at routine clinic visits. Patients may also be contacted via post by sending them a copy of the patient information sheet (see Additional file 2). Patients will be allowed a minimum of 24 hours to reflect on the content of the patient information sheet before written informed consent is obtained by completion and signing of the study-specific informed consent form (see Additional file 3).

A full list of study inclusion and exclusion criteria is given in Table 2. Subjects will be withdrawn from the trial if they choose not to continue or the investigators feel that continued participation in the trial is inappropriate. Subjects who withdraw from the intervention will be asked if they are prepared to continue to attend follow-up clinics. The study’s primary and main secondary outcomes are based on objective laboratory assays, therefore, minimising the risk of performance bias in this open-label design. Furthermore, treatment and medical management other than valaciclovir will be identical between the treated and control patients.

**Table 2 Tab2:** Study inclusion and exclusion criteria

Inclusion criteria	
	Documented diagnosis of granulomatosis with polyangiitis (Wegener’s), microscopic polyangiitis or renal limited vasculitis according to Chapel Hill Consensus Conference Criteria
	In stable remission (no documented clinical disease activity) for at least 6 months prior to study entry
	On maintenance immunosuppression with prednisolone, mycophenolate mofetil or azathioprine alone or in combination (maximum two agents)
	Documented past evidence (any time point) of CMV infection (CMV-specific immunoglobulin G detected in peripheral blood)
	Documentation that female patients of child-bearing potential are not pregnant and are using an appropriate form of contraception
	Written informed consent for study participation
Exclusion criteria	
	Stage 5 CKD (estimated glomerular filtration rate (eGFR) <15 ml minute^-1^ 1.73 m^-2^); tests performed within 6 months of pre-baseline visit can be used for this assessment
	Other significant chronic infection (HIV, hepatitis B, hepatitis C or tuberculosis)
	B-cell depleting therapy within 12 months or T-cell depleting therapy within 6 months
	Treatment with anti-CMV therapies in the last month
	Underlying medical conditions, which in the opinion of the investigator place the patient at unacceptably high risk for participating in the study
	Inability to participate fully or appropriately in the study

### Schedule of assessments

Patients will attend for a total of 14 visits over a period of just over 12 months (Fig. 1). Evaluation of CMV reactivation by deoxyribonucleic acid (DNA) PCR of blood and urine will be done monthly. Evaluation of the tolerability of the drug and adverse events will occur monthly. Immune assessments as detailed below and in Table 1 will be performed at entry, 6 months and 12 months (Fig. 1).

**Fig. 1 Fig1:**
[figure not shown]
SPIRIT figure showing study’s schedule of enrolment, intervention and assessment. *M0* baseline visit, *M1* to *M12* month 1 to month 12, *qPCR* quantitative polymerase chain reaction. *Safety blood tests will be performed only on treatment group

After providing written informed consent, the patients will undergo an initial pre-baseline visit. During this visit, a 5-ml blood sample will be drawn, which will be used to determine the percentage of CD4 + CD28null cells. This value will be utilised in the randomisation of patients as explained below.

At the baseline, 6-month and 12-month visits, a total of 50 ml of blood will be drawn in addition to a 50-ml sample of urine. The samples will be used to determine CMV viral copies by DNA PCR in blood and urine (primary outcome), the proportion of CD4 + CD28null cells in peripheral blood by flow cytometry (secondary outcome), the concentration of soluble markers of inflammation (Table 1) in peripheral blood (secondary outcome) and immune assessments and T-cell phenotyping as detailed in the exploratory outcomes (Table 1). Excess sample will be stored appropriately. Blood pressure and arterial stiffness measurements will also be carried out at the baseline, 6-month and 12-month visits as detailed below.

During the remainder of the monthly visits, a 10-ml blood sample will be drawn in addition to a 50-ml sample of urine, which will be used to determine CMV viral copies by DNA PCR in blood and urine (primary outcome). Excess sample will again be stored appropriately. In addition, safety blood tests as defined below will be performed monthly for the duration of treatment for those patients randomised to receive the drug.

Appointments will be scheduled on monthly with an allowance of 10 days either side of the estimated due date of the monthly appointment to allow for patient convenience and flexibility. The overall treatment period (or control period) of 6 months will also be subject to the same 10-day rule to avoid excessive movement of the length of treatment.

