### Randomisation

Randomisation will be undertaken using the independent telephone-based randomisation system of the Primary Care Clinical Research and Trials Unit at the University of Birmingham (which is fully accredited by the NIHR as a trials unit). We will employ block randomisation by CD4 + CD28null cell percentage stratification (cut-off 40 %). The randomisation will use mixed blocks of random size (two, four or six) not known to the research team, therefore, minimising any risk of selection bias.

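### CD4+CD28null percentage is read twice before treatment, but the only stated use of the first reading is stratification, a small missed gain in precision on a secondary outcome

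*Protocol article*

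**What the plan says.** The text under Fig. 1 in Schedule of assessments describes a pre-baseline visit after consent: "During this visit, a 5-ml blood sample will be drawn, which will be used to determine the percentage of CD4 + CD28null cells". It continues: "This value will be utilised in the randomisation of patients as explained below". The Randomisation section gives that use: "We will employ block randomisation by CD4 + CD28null cell percentage stratification (cut-off 40" %).

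The same marker is measured again at M0. The text under Fig. 1 says "At the baseline, 6-month and 12-month visits, a total of 50 ml of blood will be drawn", and lists among the uses of these samples "the proportion of CD4 + CD28null cells in peripheral blood by flow cytometry (secondary outcome"). The figure legend ties the word baseline to one visit: "M0* baseline visit, *M1* to *M12* month 1 to month 12". The visit count agrees with this: "Patients will attend for a total of 14 visits over a period of just over 12 months", which is one pre-baseline visit plus the 13 visits M0 to M12.

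Table 1 defines the secondary outcome as "Change in the proportion of CD4 + CD28null cells from baseline to 6 months". The section on sample size and planned analyses says that secondary outcomes will be compared between groups on absolute measures, with change from entry to end of treatment examined within groups. It leaves the full detail to a statistical analysis plan.

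**The concern.** Each patient has two readings of the same quantity before any treatment. The change outcome is anchored to the second. The first survives, as far as the article says, only as above or below 40 %. Assay error and short-term fluctuation in the single M0 reading then pass in full into each patient's change, while a second reading that could dampen that noise is already in hand.

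This outcome tests whether suppressing CMV reduces the CD4+CD28null expansion, and there are only 25 patients per arm. What is at stake is the width of the confidence interval for that effect.

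**Working it through.** **The plan's own figure.** The only sample size given is for CMV reactivation: 90 % against 50 %, 80 % power, two-sided 5 %. The usual two-proportion formula gives (1.96·√0.42 + 0.8416·√0.34)² / 0.4² = 19.4, so 20 per arm. With the continuity correction it is 24.1, so 25 per arm and 50 in total, which reproduces the plan. This figure does not bear on the CD4+CD28null outcome, for which no power, standard deviation or correlation is given.

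**Inputs for the present point (all correlations are assumptions).** Take every reading to have variance 1. Let r0 be the correlation between the two pre-treatment readings, r1 that between M0 and month 6, and r2 that between pre-baseline and month 6.

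**Formulas, with r2 = r1.**
- Change score, M0 alone: 2 − 2·r1. Mean of both: 1 + (1 + r0)/2 − 2·r1.
- ANCOVA residual variance, M0 alone: 1 − r1². Both readings, or their mean: 1 − 2·r1²/(1 + r0).

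**Case A: all correlations equal to r.** The change-score variance goes from 2(1 − r) to 1.5(1 − r), a fall of 25 % at any r.

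| r | ANCOVA, M0 alone | ANCOVA, both | Fall in variance | Fall in SE |
|---|---|---|---|---|
| 0.5 | 0.750 | 0.667 | 11 % | 6 % |
| 0.7 | 0.510 | 0.424 | 17 % | 9 % |
| 0.9 | 0.190 | 0.147 | 22 % | 12 % |
| 0.95 | 0.0975 | 0.0744 | 24 % | 13 % |

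**Case B: readings close in time agree better than readings six months apart.**

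| r0 | r1 | Change score: fall in variance | ANCOVA: fall in variance |
|---|---|---|---|
| 0.90 | 0.8 | 12.5 % | 9.4 % |
| 0.90 | 0.7 | 8.3 % | 5.1 % |
| 0.95 | 0.8 | 6.2 % | 4.6 % |
| 0.98 | 0.8 | 2.5 % | 1.8 % |
| 0.99 | 0.9 | 2.5 % | 2.1 % |

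**Case C: M0 also tracks month 6 better than the earlier reading does.** Take r0 = 0.97, r1 = 0.90, r2 = 0.88.
- Change score: M0 alone gives 2 − 1.80 = 0.200. The mean gives 1 + 0.985 − 0.90 − 0.88 = 0.205, a small loss.
- ANCOVA on the mean: 1 − 0.89²/0.985 = 0.196, against 0.190 for M0 alone. This is also a small loss.
- ANCOVA with both entered separately: 1 − (0.81 + 0.7744 − 2·0.90·0.88·0.97)/(1 − 0.97²) = 0.189. The model chooses its own weights, so residual variance cannot rise.

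**Price of the extra covariate.** With 50 patients and normally distributed covariates, estimating k slopes inflates the variance of the treatment effect by a factor 1 + k/(47 − k). That is 1 + 1/46 for one covariate and 1 + 2/45 for two, a ratio of 1.022. Entering both readings therefore costs about 2 %. This takes a little from the gains in Case A and the upper part of Case B, and cancels the gain at the bottom of Case B. In Case C, entering both separately ends about 2 % worse than M0 alone. The mean uses one slope and avoids this cost.

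**Unadjusted comparison of 6-month values.** Baseline does not enter it, so a second baseline reading changes nothing.

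**The case against.** The strongest reply is that the article nowhere says the first reading is used solely for randomisation. A reader might infer that it is discarded, but that is a reading of silence. A statistical analysis plan is promised, and it could define baseline as a mean or use the stratification value as a covariate. This stands, and limits the point to what the article states. It does not remove it. The article does tie baseline to M0, and for pulse wave velocity, an exploratory outcome, it does specify averaging three recordings. It says nothing comparable for the higher-ranked CD4+CD28null outcome.

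Second, the between-group analysis as written uses absolute measures. An unadjusted comparison at 6 months gains nothing from a better baseline. This also stands: the benefit comes only with a baseline-adjusted or change-based comparison. Table 1 does name change as the outcome, so such a comparison is within the plan's intent.

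Third, a reader might take the 25 % figure as what the plan gives up. It needs readings close together to be no more alike than readings six months apart. With all 14 visits in just over 12 months, the pre-baseline visit appears to fall shortly before M0, so the smaller figures in Case B are quite possible. A simple mean can even lose a little (Case C).

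Finally, stratifying at 40 % already limits chance imbalance on this marker, and the assays are to be validated for precision before the trial starts. Both are fair, and neither makes use of the continuous first reading.

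**Conclusion.** The point holds as a modest missed efficiency on one secondary outcome and its 12-month follow-on. Before the 2 % price of a second covariate, ANCOVA variance falls by about 11–24 % under equal correlations of 0.5–0.95. It falls by about 2–9 % if the two pre-treatment readings correlate at 0.90–0.99 and the 6-month correlation is 0.7–0.9. At the low end the practical gain is close to nil. The article gives nothing from which to choose between these cases.

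A reader might go further and infer that the treatment comparison is biased or the outcome wrongly defined. The documents do not support that. A single named baseline visit is a valid choice. The first reading stratifies patients and does not select them, so neither using it nor leaving it out creates a regression-to-the-mean difference between arms. The primary outcome and the sample size of 50 are untouched.

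**What to change.** State, before the analysis plan is approved, that the arms will be compared on the 6-month and 12-month CD4+CD28null percentage by ANCOVA, with the M0 value and the continuous pre-baseline value as covariates. Their mean may be used as a single covariate if the two samples are run by the same assay and lie close in time. If one reading is missing, use the other. Choose between the two forms in advance, from assay-validation or other data external to the trial comparison. Leave the stratified randomisation unchanged.

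The cost is a sentence or two of text, one extra covariate (none if the mean is used), and holding the pre-baseline percentage in the trial database, measured by the same assay as at M0. No new patients, visits or samples are needed.
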